### Compliance strategy

2.10

To maximize subjects’ compliance, we will try to prevent dropouts by providing ongoing support to patients. A direct telephone line set up for this clinical trial will enable the study team to communicate personally with the patients. Participants will be offered reimbursement to cover travel expenses for their study visits: up to ¥100/visit will be provided and total travel expense will be up to ¥700. If a patient is lost to follow-up, we will call to ask the reason and attempt to schedule a meeting at the patient's convenience.

### Randomization and blinding

2.11

In this trial, a complete randomization is adopted. Eligible subjects are randomly assigned to groups A, B, C, or D. The specific method is as follows:

1.The numbers of the observed cases are each labeled “No. 001-160.”2.Using SAS 9.0, a biostatistics expert develops a computing procedure statement with set seeds, and a random number table is generated. Based on the table, a series of random numbers emerges and these are matched individually with each case number.3.Subjects are divided into groups A, B, C, and D at the ratio of 1:1:1:1.4.According to the case number and grouping, each subject is provided with the appropriate kit, with a drug number matching the case number.5.Based on the case number, random number and grouping, emergency sealed envelopes are prepared and sent to the hospitals involved in the trial. The outside of each envelope is marked with the case number.6.When a qualified subject is enrolled into the trial, the kit with the appropriate case number, in the order of subject enrollment, is provided.

The 1st blinding is case number matching groups, that is, group A, B, C, or D. The 2nd blinding is the disposal among the 4 groups. The blinding are sealed separately, duplicated, and stored in the research unit and the pharmaceutical factory. Once the blinding is broken, the patient will be managed as off-trial.

### Statistical analysis

2.12

Statistical analyses will be conducted in 3 populations. The statistical analyses are planned to conduct in 3 populations. The intent-to-treat (ITT) population consist all randomized population who take at least 1 dose of medication and at least 1 primary efficacy evaluation on treatment. The fully evaluated (FE) population include all randomized patients who have receive at least 80% assigned 24 weeks’ double-blind medication with complete record of efficacy variable, with no major protocol violations. The safety set population included all randomized population and receive at least 1 dose of the study medication, with at least 1 safety record post baseline.

The efficacy analysis will be conducted with the ITT population and FE populations, for the VADAS-cog and CDR-SB will be analyzed by using the Last Observation Carried Forward method for the replacement of missing observations.

Multivariate analysis of covariance (ANCOVA) models that included baseline score as covariate, treatment, and center were used to assess differences between the treatment groups for linear efficacy measures. Categorical efficacy assessments were analyzed with a Cochran–Mantel–Haenszel test. The least squares mean changes from baseline scores to endpoint were presented for variables analyzed with the ANCOVA models. All values were 2-tailed, and all analyses were significant if the value was ≤0.05.

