### Evaluation time point

2.6

The efficacy measurement will be assessed at baseline (week 0), at the midpoint (week 4 and week 12), and at the endpoint (week 24), 12 weeks after withdrawal (week 36).

The safety assessments will be evaluated at the baseline (week 0), at the midpoint (week 4, week 8, and week 12), and at the endpoint (week 24).

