### Study drug termination criteria

2.9

1)Prior to the maximum treatment period of 24 weeks, study drug will be discontinued if any of the following conditions are met:2)Patient or informant request termination of study drug;3)Patient or informant withdraws consent for the study;4)Noncompliance with study drug as determined by the investigator (patients who have taken 80% or more of the expected number of tablets will be considered compliant);5)Decision by the investigator that the study drug should be discontinued on safety grounds;6)The reason for study drug termination should be recorded and any unused medication returned to pharmacy.

After the protocol is approved by the Ethics Committee, if modified, it must be reported to the Ethics Committee before execution and also recorded in the drug administration department.

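### The efficacy set labelled ITT is a modified ITT: randomised patients who never take a dose, or who stop drug before the week-4 visit, are in no efficacy analysis

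*Protocol article*

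**What the plan says.** All references are to the protocol article.

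- **Efficacy sets (Statistical analysis, 2.12).** The ITT population is "all randomized population who take at least 1 dose of medication and at least 1 primary efficacy evaluation on treatment". The second set, FE, is limited to randomised patients who "have receive at least 80% assigned 24 weeks’ double-blind medication with complete record of efficacy variable" and who have no major protocol violation. "The efficacy analysis will be conducted with the ITT population and FE populations"; no analysis of all randomised patients is named.
- **Missing data (2.12).** VADAS-cog and CDR-SB are "analyzed by using the Last Observation Carried Forward method for the replacement of missing observations".
- **Visits (Evaluation time point, 2.6).** Efficacy is measured at weeks 0, 4, 12 and 24, and at week 36 after withdrawal of drug.
- **Unblinding (Randomization and blinding, 2.11).** "Once the blinding is broken, the patient will be managed as off-trial".
- **Safety set (2.12).** Randomised patients who took at least one dose, "with at least 1 safety record post baseline".

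**The concern.** An intention-to-treat comparison keeps every randomised patient in the assigned arm, because only randomisation makes the arms comparable. Here membership depends on two later events: taking a dose, and being evaluated while on treatment. Read literally, the second condition is stricter than the usual requirement of one post-baseline value. A patient who stops drug in week 2 and is then assessed at weeks 4, 12 and 24 would still be outside the set.

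If early stopping is related to dose, the arms that are analysed are no longer the arms that were randomised, and the less tolerated arm looks better than it is. This matters because the trial is meant to supply evidence on the effective dose (Discussion).

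The unblinding rule adds to the problem. If off-trial status ends scheduled assessments, a patient unblinded before week 4 never acquires the qualifying evaluation. One unblinded later contributes only a carried-forward score.

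**Working it through.** **Who is left out**

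| Patient | ITT as defined | FE | Any efficacy analysis |
|---|---|---|---|
| Randomised, never dosed | out | out | none |
| Dosed, stops drug before week 4, not assessed again | out | out | none |
| Dosed, stops drug before week 4, assessed later | out (literal reading) | out | none |
| Stops after an on-treatment evaluation | in, by carry-forward | depends on the FE criteria | yes |
| Unblinded after an on-treatment evaluation | in; no set excludes for unblinding | depends on the FE criteria | yes, later scores probably missing |

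**Could early loss differ by arm?** A tablet contains 14 mg (Intervention, 2.3). The top arm takes 3 × 2 × 14 = 84 mg/d. The Introduction gives 84 mg/d as the maximum tolerated dose in healthy people. This makes a difference between arms plausible but does not give a rate. The 20% discontinuation in Sample size (2.7) is not split by arm or by time.

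**The plan's own figure.** I used a one-way F test with 4 groups, noncentrality n × 4 × V / SD², degrees of freedom 3 and 4(n − 1). Inputs as stated in 2.7: V = 1.14, SD = 7.44, two-sided α = 0.20. At n = 32 the power is 0.506, so the stated 32 per group is reproduced. Enrolling 40 per arm leaves 40 × 0.80 = 32 after 20% loss.

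**Power.** With the same inputs:

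| Excluded | n per arm | Power |
|---|---|---|
| 0% | 40 | 0.57 |
| 5% | 38 | 0.56 |
| 10% | 36 | 0.54 |
| 15% | 34 | 0.52 |
| 20% | 32 | 0.51 |

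The loss of power is small, so the issue is bias.

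**Bias.** The planned changes are −0.25 for placebo and 2.25 for the top arm, a difference of 2.25 − (−0.25) = 2.50. Assumptions, none of them in the documents:

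- a fraction d of the top arm leaves before week 4, and none of the placebo arm does;
- patients who stay have the planned means;
- those who leave would have changed like placebo (−0.25).

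As-randomised difference = (1 − d) × 2.25 + d × (−0.25) − (−0.25) = 2.50 − 2.50d. Overstatement = 2.50d.

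| d | Patients of 40 | As-randomised difference | Overstatement |
|---|---|---|---|
| 0.05 | 2 | 2.375 | 0.125 |
| 0.10 | 4 | 2.250 | 0.250 |
| 0.15 | 6 | 2.125 | 0.375 |

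If those who leave would have done worse, say −3.75 (also an assumption), the overstatement is d × 6.00: 0.05 × 6.00 = 0.30 to 0.15 × 6.00 = 0.90. If early loss is equal across arms and unrelated to outcome, it is about zero.

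**Scale.** The standard error of a two-arm difference is 7.44 × √(2/40) = 1.66. The main range is 0.125/1.66 = 0.08 to 0.375/1.66 = 0.23 standard errors.

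**The case against.** An efficacy set that needs one dose and one evaluation is common in a small double-blind phase IIa trial, and *on treatment* may only mean during the treatment period. That is fair. On the looser reading, a patient who stopped drug but attended week 4 would count. Patients never dosed or never assessed would still be lost, the label would still be wrong, and the text does not say which reading applies. A fuller analysis plan may add an all-randomised analysis, but the definition printed here would still need correcting.

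The illustrated bias is also small beside the standard error, and its upper end puts 6 of 40 patients in one arm out early with none on placebo. That stands, and it limits the weight of the point.

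A reader might infer more than the text supports:

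- **That tolerability dropouts in general leave the ITT analysis.** They leave it only before a first on-treatment evaluation. Later ones stay by carry-forward.
- **That unblinded patients are removed from the analysis.** Section 2.11 speaks of how the patient is managed, and no set in 2.12 excludes for unblinding. The likely effect is lost assessments.
- **That the noncompliance rule in 2.9 removes patients from ITT.** It is a reason to stop drug. The 80% criterion in 2.12 defines FE.
- **That the safety set hides harm.** Adverse events are part of the safety assessment (2.5), so a patient who stops with a recorded event stays in. Dropping dosed patients with no later record shrinks the denominator and raises the event rate.

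**Conclusion.** The point holds in a limited form. The set is mislabelled: it is a modified ITT, and randomised patients who never dose or who stop drug before week 4 are in no efficacy analysis. That follows directly from 2.12 and 2.6, subject to the literal reading of *on treatment* for those assessed after stopping.

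The size is uncertain. Under the stated assumptions (5-15% early loss in the top arm only, placebo-like change in those lost), the 2.50-point difference is overstated by about 0.13-0.38 points, or 5-15% of it. It is about zero if early loss is equal and non-informative. The documents give no arm-specific or early rate that would settle this.

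The off-trial rule is a contributing weakness, because it is likely to end assessments; it is not an exclusion from the set. The point is of moderate weight and should be settled before the data are unblinded.

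**What to change.** 1. Analyse all randomised patients in their assigned arm. Alternatively, rename the present set modified ITT and add the all-randomised analysis beside it.
2. Delete the on-treatment condition, so that any post-baseline score counts whether or not the patient is still taking drug.
3. Add a sensitivity analysis that gives patients without post-baseline scores placebo-like or unfavourable values.
4. State in 2.11 and 2.9 that patients who are unblinded or who stop drug continue scheduled assessments and stay in the analysis unless consent is withdrawn. The criteria for stopping drug are not affected.
5. As a minor point, define the safety set as all who took at least one double-blind dose.

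The cost is wording, one added analysis and some effort to follow patients at visits already on the schedule. The telephone contact described in Compliance strategy (2.10) would help, though the documents do not cost this follow-up. The downside is that the effect estimate may be slightly diluted.

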### Efficacy measurements

2.4

The primary efficacy measurements are changes of the vascular dementia assessment scale-cognitive subscale (VADAS-cog/17 items)^[9]^ and the clinical dementia rating-sum of the boxes (CDR-SB)^[10]^ scale from baseline to the 24th week after treatment. VADAS-cog is a revision of the ADAS-cog to be a better measure in vascular conditions,^[11]^ and a higher score indicates higher impairment. In addition to ADAS-cog, the VADAS-cog comprises additional frontal lobe tests reflecting attention, working memory, executive function, and verbal fluency.^[9]^ It was suggested that the VADAS-cog may be a more sensitive endpoint in patients with white matter load and vascular burden of the brain than ADAS-cog.^[12]^

The CDR-SB is a standard for disease grading in clinical studies of dementia and is used for overall endpoint assessment in clinical trials. It comprehensively assesses the cognitive and functional aspects of dementia patients, including memory, orientation, judgment and problem-solving skills, social affairs, family and hobbies, and personal cooking. The CDR-SB scores from 0 to 18 points, and a higher score indicates higher impairment.

The secondary efficacy measurements include the MMSE and ADL scale.^[6,13]^ The MMSE is used to assess the global cognition. ADL was used to measure the physical self-maintenance ability and instrumental ADL ability.^[13,14]^

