### Sample size

2.7

There are no similar studies using TMBCZG tablets to treatment patients with VaD for the proposed study duration (24 weeks). The sample size was calculated based on the primary endpoints, VADAS-cog. It is hypothesized that the efficacy of TMBCZG in the treatment of mild to moderate VaD is similar to that of donepezil. Previous studies reported that the mean changes of ADAS-cog scores after 5 and 10 mg donepezil treatment were (5.75 ± 7.44) points and (2.25 ± 7.44) points, respectively. We assume that the placebo control group has a certain progression after 24 weeks’ treatment (△ = −0.25). The mean scores of the 3 groups of VADAS-cog scale improvement were set at equal intervals, that is, the changes before and after the scores of each group were −0.25, 0.75, 1.50, 2.25, and the variance of the 4 groups of VADAS-cog means 1.14. The standard deviation within is 7.44 points. For this phase IIa study, the 2-sided test level α = 0.20 and the power 1-β = 0.50. This clinical trial adopts a balanced design and uses nQuery Advisor 7.0 to calculate, 32 cases are needed for each group. Considering a greater rate of discontinuation of 20%, the sample size was increased to 39 per group to ensure adequate patients to complete the study. The total number of cases was 160 cases, that is, 40 cases in the placebo control group and 40 cases in the 3 dose groups of the TMBCZG tablets. Note also that because this study is a pilot efficacy study (phase IIa), a larger sample size to reach a higher degree of statistical power is not required.

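### LOCF with endpoint ANCOVA on both primary scales does not target the week-24 change it is meant to estimate; the planned visits already allow a repeated-measures model (should fix)

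*Protocol article*

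**What the plan says.** Section 2.4 (Efficacy measurements) defines both primary measures, VADAS-cog and CDR-SB, as change on the "scale from baseline to the 24th week after treatment". Section 2.6 (Evaluation time point) sets the visits: "The efficacy measurement will be assessed at baseline (week 0), at the midpoint (week 4 and week 12), and at the endpoint (week 24"), followed by an off-drug visit at week 36.

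Section 2.12 (Statistical analysis) fixes the handling of missing data: VADAS-cog and CDR-SB "will be analyzed by using the Last Observation Carried Forward method for the replacement of missing observations". The model is ANCOVA with baseline, treatment and center, and it has no visit term. Efficacy is analysed in two sets. ITT requires "at least 1 primary efficacy evaluation on treatment". The fully evaluated (FE) set requires at least 80% of medication taken, "with complete record of efficacy variable, with no major protocol violations".

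Section 2.7 (Sample size) plans week-24 mean changes of -0.25, 0.75, 1.50 and 2.25 (positive is improvement; the placebo arm is taken to progress). It also allows for dropout: "Considering a greater rate of discontinuation of 20" percent.

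**The concern.** LOCF treats a patient last seen at week 4 or 12 as if the score would be unchanged at week 24. The sample-size section assumes the opposite, since every arm changes over the 24 weeks. If a benefit is still building when patients leave, carrying the earlier score forward dilutes it. If arms lose patients at different rates, the shared time course is cut short more often in one arm, and that alone can create or hide a difference.

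Equal dropout cannot be taken for granted. By section 2.3 the high-dose arm takes 3 × 14 mg × 2 = 84 mg/d, which is the figure the Introduction gives as the maximum tolerated dose in healthy persons. I draw nothing from this about the dose, only that discontinuation may differ by arm. The Discussion says the trial should supply evidence on the effective dose, so distortion between dose arms matters as well as distortion against placebo.

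**Working it through.** **The plan's own figure.** Four-group F test, variance of means 1.14, SD 7.44, two-sided α 0.20, 32 per group: noncentrality = 4 × 32 × 1.14 / 7.44² = 145.92 / 55.35 = 2.64, power 0.506. The stated 32 reproduces. With dropout, 32 × 1.2 = 38.4, giving 39; 32 / 0.8 = 40; 40 per arm are enrolled.

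**Which value is carried.** ITT needs one on-treatment evaluation, and the scheduled visits before week 24 are weeks 4 and 12. The carried score therefore comes from one of those two.

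**Expected LOCF change per arm, dropout unrelated to score:**

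μ₂₄ × [(1 − d) + d × (q·f₄ + (1 − q)·f₁₂)]

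Here d is dropout, q is the share of dropouts last seen at week 4, and f₄ and f₁₂ are the fractions of the week-24 change reached by weeks 4 and 12. From the article: μ₂₄ = 2.25 (high dose) and -0.25 (placebo), true difference 2.50, and overall dropout of 20%. Assumed: f₄, f₁₂, q, the split of dropout by arm, and that every dropout has a post-baseline visit.

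Example, linear course (f₄ = 4/24, f₁₂ = 12/24), d = 0.20, q = 0.5: retained fraction = 0.8 + 0.1 × 4/24 + 0.1 × 12/24 = 0.867, so 2.50 becomes 2.167.

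Expected high-dose minus placebo difference at q = 0.5 (range for q from 1 to 0):

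| Assumed course (f₄, f₁₂) | 20% / 20% dropout | 10% placebo / 30% high | 30% placebo / 10% high |
|---|---|---|---|
| Linear (1/6, 1/2) | 2.167 (2.083–2.250) | 2.033 (1.917–2.150) | 2.300 (2.250–2.350) |
| Plateau by week 12 (0.5, 1) | 2.375 (2.250–2.500) | 2.325 (2.150–2.500) | 2.425 (2.350–2.500) |
| Late (0.05, 0.25) | 2.075 (2.025–2.125) | 1.905 (1.835–1.975) | 2.245 (2.215–2.275) |

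The bias runs from 0 to 1.835 − 2.50 = -0.665 points (-27%).

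**Between doses.** Linear course, q = 0.5, 30% dropout on high dose and 20% on middle dose: 2.25 × 0.80 = 1.80 and 1.50 × 0.867 = 1.30. The planned gap of 0.75 becomes 0.50.

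**Inactive drug, 10% placebo and 30% active dropout.**
- Both arms worsen 3 points linearly (assumed), q = 0.5: placebo -3 × 0.933 = -2.8, active -3 × 0.80 = -2.4, false benefit 0.4. With the placebo arm's own -0.25 in place of 3 points it is only 0.03. If placebo has the higher dropout, the sign reverses.
- An early gain of 1 to 2 points (assumed) followed by the planned -0.25: (0.30 − 0.10) × (1.25 to 2.25) = 0.25 to 0.45.

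**Simulation with dropout depending on observed scores** (40 per arm, 4000 runs, true difference 2.5). For the linear course, mean LOCF was 2.16 (20/20), 1.75 (10/30) and 2.52 (30/10). Over all three courses it ran from 1.59 (late, 10/30; complete data 2.46) to 2.67 (plateau, 30/10; complete data 2.51). A likelihood repeated-measures estimate stayed between 2.44 and 2.54. For an inactive drug with both arms worsening 3 points and 10/30 dropout, LOCF gave 0.17 and repeated measures -0.05. The standard error was 1.66 to 1.72 for LOCF and 1.76 to 1.82 for repeated measures.

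**Scale.** The standard error of a pairwise difference is 7.44 × √(2/40) = 1.66. The linear 20/20 loss is 0.33 / 1.66 = 0.2 standard errors.

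**The case against.** The strongest reply is that the effect on the trial's conclusion is small. In a separate simulation of a linear dose contrast (about 19% score-dependent dropout), mean z was 1.43 under LOCF and 1.47 under likelihood. That is power of about 0.30 against 0.31 at the 0.05 level, or 0.56 against 0.58 at the design's 0.20. A false benefit of 0.25 to 0.45 points is 0.15 to 0.27 standard errors and moves a 5% error rate to about 5.3% to 5.8%. Section 2.7 describes a phase IIa pilot with power 0.50. This stands, and it limits the severity.

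It also stands that not all of the 20% would be carried forward. Patients who leave before week 4 fall out of ITT. If a quarter of the dropouts do so, the retained fraction in the linear example is 1 − (15/95) × 2/3 = 0.89; if half do, it is 1 − (10/90) × 2/3 = 0.93.

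Three stronger readings might be inferred, and the article supports none of them.
- *LOCF certainly biases the result, in a known direction.* The article gives only week-24 means, with no time course and no dropout by arm. The bias can be nil, and under score-dependent dropout slightly positive.
- *The standard error is wrong.* The last observed score is a function of observed data, and ANCOVA gives an essentially ordinary standard error for its mean difference. The fault is in the quantity estimated. No coverage failure has been shown.
- *The FE set offers no check.* It needs complete records, so it is an analysis with little or no imputation, and a gap from ITT would be informative. It is an imperfect check because completers are selected.

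A condensed article may leave missing-not-at-random sensitivity analyses to a plan not shown here, so their absence is no finding. The choice of LOCF is different, because the article states it.

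**Conclusion.** The point holds as a should-fix. The stated method analyses ITT patients without a week-24 score at their week-4 or week-12 value, so it estimates a mixture of time points in place of the week-24 change, unless scores have plateaued by the last visit or the distortions happen to cancel. On an assumed linear course with 20% dropout per arm, 2.50 points becomes about 2.1 to 2.25. Across the assumed courses and splits, with dropout unrelated to score, the bias is 0 to about -0.67 points; score-dependent dropout widened this to between about -0.87 and +0.16 against complete data. Unequal dropout can produce a false benefit of about 0.2 to 0.45 points for an inactive drug if scores move appreciably over the 24 weeks.

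These are modest beside a standard error of about 1.7 and would rarely change the trial's conclusion alone. The argument is validity: the distortion is systematic, falls on both primary scales, and cannot be assumed conservative.

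**What to change.** Before unblinding, make the primary analysis in the ITT set a mixed model for repeated measures on change at weeks 4, 12 and 24. Include treatment, visit, treatment × visit, baseline, baseline × visit and center, with unstructured covariance and the week-24 contrast as primary. Three visits need six covariance parameters, which 160 patients can support. Leave the off-drug week-36 visit out of this model. Keep LOCF ANCOVA as a sensitivity analysis and describe FE as a completer analysis.

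Costs:
- No new data are needed, but the trial is described as ongoing. Section 2.9 requires modifications to be reported to the Ethics Committee before they are carried out and recorded with the drug administration department.
- The standard error is somewhat larger (about 1.8 against 1.7).
- The model assumes data are missing at random. A sensitivity analysis for departures from that belongs in the statistical analysis plan.
- Patients lost before week 4 stay excluded by the ITT definition; this change does not repair that.

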## Discussion

3

*Gastrodia elata* (Tianma in Chinese), usually used to treat ischemic stroke, epilepsy, dizziness, and dementia for centuries in China in traditional Chinese medicine. TMBCZG is the active ingredient, which is extracted from *G elata*; studies have showed that gastrodin is effective in the treatment of bilateral common carotid artery occlusion-induced VaD via targeting Aβ-related protein formation and inhibiting autophagy and apoptosis of hippocampus neurons, ameliorates sub-acute phase cerebral ischemia reperfusion injury by inhibiting inflammation and apoptosis in rats^[15]^. However, there is no clinical trial on the treatment of VaD with TMBCZG tablets.

Studies showed that the most impaired cognitive domains in patients with VaD were attention/psychomotor speed, executive function, visuo-spatial (maze and structural tests in VADAS-cog), and language (animal fluency test). So we used the VADAS-cog scale as the primary efficacy measurement. And the neuropsychologic battery in this study covered these important domains comprehensively.

This ongoing randomized, double blind, parallel Group, placebo controlled, multicenter, 24-week clinical trial will be the 1st rigorous testing of TMBCZG tablets for the treatment of patients with VaD. Success in this clinical trial will provide evidence for the use of TMBCZG tablets in the treatment of VaD, and supply evidence of effective dose of TMBCZG in VaD.

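### The trial is sized at two-sided alpha 0.20 but judged at 0.05; at 0.05 the protocol's own inputs give about 24% power with 32 per group, not 50%

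*Protocol article*

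**What the plan says.** Section 2.7 (Sample size) bases the calculation on VADAS-cog. Its inputs are:

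- level and power: "the 2-sided test level α = 0.20 and the power 1-β = 0.50";
- mean changes: "the changes before and after the scores of each group were −0.25, 0.75, 1.50, 2.25";
- spread of those means: "the variance of the 4 groups of VADAS-cog means 1.14";
- within-group spread: "The standard deviation within is 7.44 points".

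The result is that "32 cases are needed for each group". This is raised to 39 for 20% discontinuation, and 40 per group (160 in all) are enrolled. The section adds that higher power is not required because the study is a phase IIa pilot.

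Section 2.12 (Statistical analysis) specifies ANCOVA with baseline score, treatment and center, and last observation carried forward for missing values. It ends with a two-tailed rule: "all analyses were significant if the value was ≤0.05".

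The Discussion says: "Success in this clinical trial will provide evidence for the use of TMBCZG tablets in the treatment of VaD". It adds that the trial will also supply evidence on the effective dose.

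**The concern.** Both levels are printed in the same article and both cover the primary VADAS-cog comparison, but only one can decide it. A primary p-value between 0.05 and 0.20 counts as positive at the level used for sizing and as negative at the level given for analysis. If this stays open, the threshold could be chosen after the result is known.

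The mismatch also changes what the stated power means. The 50% figure holds only for a test at 0.20. A reader who takes section 2.12 at its word would credit the trial with about twice the power it has, and could read too much into a non-significant result.

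**Working it through.** **Inputs.** All come from section 2.7: means −0.25, 0.75, 1.50, 2.25; variance of means V = 1.14; within-group SD 7.44; n = 32 needed and 40 enrolled per group; k = 4 groups. Section 2.12 supplies the level 0.05.

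**Method.** One-way F test with k − 1 = 3 and 4(n − 1) degrees of freedom and noncentrality λ = k·n·V / SD², where SD² = 7.44² = 55.35. Power is the probability that a noncentral F variable exceeds the central F critical value.

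**Step 1: reproduce the plan's figure.** λ = 4 × 32 × 1.14 / 55.35 = 2.64, with 124 denominator degrees of freedom. At alpha 0.20 the critical value is 1.57 and power is 50.6%. With 31 per group it is 49.8%. So 32 is the smallest size reaching 50%, and the global F test appears to be how the trial was sized.

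**Step 2: change only alpha to 0.05.** With n = 32, λ is still 2.64, the critical value rises to 2.68, and power is 23.8%. With n = 40, λ = 4 × 40 × 1.14 / 55.35 = 3.30 and power is 29.3%. At this level, 50% power would need 71 per group.

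**Step 3: check the variance of the means.** The mean of the four values is 4.25 / 4 = 1.0625. The squared deviations are 1.7227 + 0.0977 + 0.1914 + 1.4102 = 3.4219. Dividing by 3 gives 1.14, the printed value; dividing by 4 gives 0.86 (0.8555). The noncentrality is n·Σ(deviation²) / SD², so with λ = k·n·V / SD² the divisor must be k = 4. This is a separate error from the mismatch in levels.

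**Step 4: power under each combination.**

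| Variance of means | n per group | λ | Power at 0.20 | Power at 0.05 |
|---|---|---|---|---|
| 1.14 (as printed) | 32 | 2.64 | 50.6% | 23.8% |
| 1.14 (as printed) | 40 | 3.30 | 57.0% | 29.3% |
| 0.8555 (divisor 4) | 32 | 1.98 | 43.7% | 18.6% |
| 0.8555 (divisor 4) | 40 | 2.47 | 49.1% | 22.6% |

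With V = 0.8555, 50% power at 0.05 would need 95 per group.

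**Step 5: other tests that section 2.12 could cover, at 0.05.** High dose against placebo is a difference of 2.25 − (−0.25) = 2.5 points. With n = 32 the standard error is 7.44 × √(2/32) = 1.86, and power is 26% (t test) to 27% (normal approximation). With n = 40 it is 32% by either method. A linear trend across the four groups gives 28.5% and 34.4%. No multiplicity adjustment is applied to these figures.

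**Step 6: baseline adjustment.** If 7.44 is an unadjusted SD, the ANCOVA residual variance is about 7.44² × (1 − r²), where r is the correlation between baseline and change. The article gives no r. As an illustration only, r = 0.5 divides the residual variance by 1 / 0.75, and F-test power at 0.05 becomes 24% (V = 0.8555, n = 32) to 38% (V = 1.14, n = 40).

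**The case against.** The best defence is that section 2.7 openly calls this a phase IIa pilot, accepts 50% power and says more is not required. A weak negative result is thus already disclosed, and the printed decision threshold is the stricter, conventional one. That stands as a reason for choosing a small trial. It is not a reason for computing power at one level and deciding at another.

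A second defence is that 32 completers may understate the analysed number. The intent-to-treat set with last observation carried forward could keep close to 40 per group, the decision test need not be the global F test, and baseline adjustment may help. This is why a range is given. None of the alternatives computed above reaches 50% at 0.05.

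Two stronger readings are tempting, and the document supports neither.

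- **That the mismatch in levels alone cuts power to about 19%.** It does not: changing alpha alone gives about 24%. The 19% figure also needs the variance divisor corrected, and on that basis power at 0.20 was already about 44%.
- **That neither level could yield any evidence.** A test at 0.05 still holds its type I error at 0.05, however low the power. On the F-test figures, a positive result at 0.05 is about 3.7 (0.186 / 0.05) to 5.9 (0.293 / 0.05) times likelier under the assumed effect than under none. The Discussion sentence is optimistic for a pilot, but that is a minor matter of wording.

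**Conclusion.** The contradiction between sections 2.7 and 2.12 is real and nothing in the article resolves it. Read as written, the primary VADAS-cog comparison has about 24% power at 0.05 with 32 per group and 29% with 40, against the 50% stated. If the variance of the means is corrected as well, the figures are about 19% and 23% at 0.05, and 44% and 49% at 0.20.

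These values assume the global F test that reproduces the sizing, the listed means, an SD of 7.44 and no gain from baseline adjustment. A gain from adjustment is plausible but cannot be sized from the article. The finding concerns which level governs and what power goes with it; it does not mean that a pilot must be larger.

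**What to change.** Before unblinding, set one significance level for the primary VADAS-cog comparison in both 2.7 and 2.12, and restate the power at that level. Either:

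- **Keep 0.05.** State power of about 24% (32 per group) to 29% (40 per group) if the variance of 1.14 stays in the text, or about 19% to 23% if the variance is also corrected to 0.86. The printed variance and the printed power must agree.
- **Use 0.20.** State that the primary test is a phase IIa go/no-go screen at two-sided 0.20, report intervals at the matching 80% level (95% intervals may be added), and make no efficacy claim. If the variance is corrected, power is about 44% with 32 per group and 49% with 40.

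As a minor point, reword the Discussion so that success supports a larger trial rather than use in VaD.

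The change is wording in 2.7, 2.12 and the Discussion. It needs no more patients. The cost is a less favourable stated power or a more modest claim.
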